### Secondary Outcomes

Gambling and trading behaviors were assessed for frequency and intensity using items adapted from the EDADES survey [63] to capture gambling frequency and spending in both online and offline contexts. Trading behavior was assessed with items adapted from the study by Delfabbro et al [29], covering trading frequency, trading types, and frequency of monitoring financial markets. In the baseline and posttest assessments, these behaviors were measured retrospectively for the past year, while the follow-up covered the previous 3 months. Amateur or professional investment use was assessed with a dichotomous item (yes or no) regarding professional trading, as well as items on the use of broker platforms or apps.

Problem gambling was assessed using the 9-item Spanish version of the Problem Gambling Severity Index (PGSI) [66,67], categorizing participants into 4 groups: nonproblematic (PGSI=0), low-risk (PGSI=1‐2), moderate-risk (PGSI=3‐7), and problem gambling (PGSI≥8). Additionally, the Gambling Disorder Identification Test (GDIT) [68,69] was administered at follow-up as part of a planned validation process. The GDIT is a 14-item Likert scale instrument evaluating gambling behaviors, symptoms, and negative consequences. This scale allows for the classification of participants into the following categories: nongambling, recreational gambling, problem gambling, and pathological gambling (mild, moderate, or severe).

Disordered trading was measured with the Trading Disorder Scale [34], a validated 13-item instrument assessing problematic trading behaviors. The scale is based on research criteria proposed by Guglielmo et al [70], which are derived from selected *Diagnostic and Statistical Manual of Mental Disorders, Fifth Edition* (*DSM-5*) criteria for gambling disorder and internet gaming disorder [71] to conceptualize trading-related problems. This scale captures key aspects of behavioral addiction, such as tolerance, withdrawal, loss of control, craving, social impairment, and persistence despite negative consequences [34].

### Other Measures

Gambling- and trading-related harms were measured using the Short Gambling Harm Screen [72], a brief 10-item binary-response tool adapted to capture financial, emotional or psychological, and relational harms from gambling and trading. Perceived self-efficacy to resist gambling and trading urges was measured using an adaptation of the Brief Situational Confidence Questionnaire [73], which has been psychometrically validated for gambling-related behaviors in an adult general population sample [74]. This adapted version includes 2 additional items assessing confidence in resisting the urge to gamble when faced with situations involving financial pressure or the influence of alcohol or drugs, complementing the original 8 items focused on unpleasant emotions, physical discomfort, pleasant emotions, social pressure, and tests of control. Peer and family gambling and trading behaviors were assessed through ad hoc items. These items inquired about friends’ and family members’ involvement in financial trading and gambling. Finally, a 5-point Likert scale was used to evaluate satisfaction with and usefulness of the online PNF intervention (only in intervention groups).

### Data Analysis Plan

The data of the project will be made available upon reasonable request, supporting adherence to Open Science principles and ensuring transparency throughout the research process. Data will be analyzed using SPSS (version 28.0; IBM Corp), Mplus (version 8.7; Muthén & Muthén), and R (R Foundation for Statistical Computing). Descriptive analyses and group comparisons will be performed using chi-square tests for categorical variables and 2-tailed Student *t* test for independent samples, and ANOVA (including multivariate analysis of variance [MANOVA] and multivariate analysis of covariance [MANCOVA]) for continuous variables with a 95% confidence level. Data distribution will be tested with Kolmogorov-Smirnov and Shapiro-Wilk tests. If the assumption of normality is not met, nonparametric alternatives will be used. Effect sizes will be reported using appropriate statistics (eg, odds ratio, Cohen *d*, Rosenthal r, omega squared, or Cramer V). To control for type I error due to multiple comparisons, the Bonferroni correction will be applied. Results will be weighted by age, gender, and region.

To examine gambling and trading trajectories, primary longitudinal analyses will focus on generalized linear mixed models, which are preferred over traditional repeated-measures ANOVA due to their ability to handle missing data and accommodate nonnormal outcome distributions. Mixed latent class analyses will be used to identify latent subpopulations characterized by different patterns of gambling and trading intensity and severity over time. These analyses will be considered exploratory and contingent on data structure and model fit.

Mediation and moderation analyses will be conducted as secondary and exploratory analyses to examine potential mechanisms and conditional effects of the PNF intervention. These analyses will be implemented using the PROCESS macro for SPSS and structural equation modeling in Mplus to estimate direct and indirect effects, with continuous variables centered to reduce multicollinearity [75]. Bias-corrected 95% CIs will be generated from 10,000 bootstrap random samples.

During the evaluation of the PNF, observed variables will be controlled to ensure balanced baseline characteristics between control and experimental groups, thus confirming randomization integrity. Additionally, a comparative analysis will be conducted between participants who meet inclusion criteria (ie, engaging in gambling or trading activities in the past 60 days) and those who do not, assessing differences in sociodemographic variables, psychological distress, suicidal behavior, substance use, and gambling participation reported during eligibility assessment.

Questionnaires not previously validated in the Spanish population or for the constructs of interest will undergo psychometric evaluation, including item analysis, reliability, and validity testing. Item analysis will include item-test correlations, discarding items with discrimination indices below 0.30 [76]. Reliability analysis will be assessed using omega coefficients; a total omega ≥0.70 will be considered acceptable [77], while hierarchical omega will require a minimum of 0.50 per subscale [78]. Dimensionality and validity will be assessed through confirmatory factor analysis. Goodness-of-fit tests will be conducted, using the following indices and interpretations for the assessment of model fit: the comparative fit index, the relative goodness-of-fit index, the root mean square error, the Tucker-Lewis index, and the chi-square statistic corrected for degrees of freedom. A satisfactory model fit will be considered when the comparative fit index, Tucker-Lewis index, and relative goodness-of-fit index values are greater than 0.90; the root mean square error value is less than or equal to 0.05; and the chi-square statistic corrected for degrees of freedom values is close to 0 [79]. Measurement invariance will be tested across age, sex, and gambling or trading activity subgroups to confirm the stability of the factor structure across groups.

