### Sample Size Estimation

Given the lack of prior studies examining the impact of online PNF on intention to change and help seeking among individuals with gambling or trading problems, sample size estimation was based on previous trials evaluating PNF effects on gambling-related outcomes in young adults. Assuming an α error of 5%, an effect size f=0.15, and a correlation between baseline and follow-up measures of 0.5 [39,57], it was estimated that a total of 164 participants would be required to achieve a statistical power (1–β) of 90% for detecting differences within and between groups on a single outcome.

Given the evaluation of multiple outcomes, a minimum effective sample size of 328 was required. To account for potential attrition, the effective sample was adjusted using the following formula: final sample size=effective sample size/(1–loss to follow-up rate). Given the online panel setting, a conservative loss-to-follow-up rate of 50% was assumed before study launch. This adjustment yielded a target enrollment of 656 participants in total, corresponding to a minimum of 164 (25%) participants per randomized condition at baseline.

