By examining the profiles of individuals who exhibit low motivation to seek help, the study also intends to provide insights that can contribute to the refinement of treatment and prevention strategies. However, several limitations should be acknowledged. First, longitudinal studies using online panels are susceptible to high attrition rates. To mitigate this, a conservative oversampling strategy (assuming 50% loss to follow-up) was used, and missing data will be handled via generalized linear mixed models. Second, as the sample is restricted to Spanish residents, cross-cultural generalizability may be limited. Finally, given the novelty of behaviors such as cryptocurrency trading, some measures were adapted ad hoc. Rigorous psychometric analyses are planned to validate these instruments as part of the study’s contributions.

Despite these limitations, findings may inform regulatory policies for trading platforms and gambling-like activities within video games to better protect vulnerable users. Excessive engagement in these activities has been associated with other addictive behaviors, such as disordered gambling and substance use, as well as emotional difficulties [82]. Furthermore, increased engagement in financial markets has been linked to rising suicide rates among both amateur and professional investors [70]. Consequently, the outcomes of the study are expected to advance public health by elucidating the psychological and social consequences of these converging behaviors and supporting the development of effective, scalable interventions aimed at reducing harm and facilitating help seeking in this population.

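### No baseline-adjusted or longitudinal model is named for the primary outcomes: the two 0-100% items fall to a normality-gated group test, and mixed models are tied by name only to the secondary behaviours

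*Protocol article*

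**What the plan says.** All references are to the protocol article.

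- **Primary outcomes.** The Abstract makes intention to change and help-seeking primary, and gambling and trading behaviours with their trajectories secondary. Under Primary Outcomes, three items are described as repeated at pretest, posttest and 12 weeks: the likelihood of gambling or trading (0-100%), the likelihood of seeking treatment (0-100%), and a three-category plan to reduce or stop.
- **Group comparisons.** The Data Analysis Plan uses chi-square for categorical variables and t test, ANOVA, MANOVA or MANCOVA for continuous ones. Kolmogorov-Smirnov and Shapiro-Wilk tests are applied, and "If the assumption of normality is not met, nonparametric alternatives will be used".
- **Mixed models.** The same section says: "To examine gambling and trading trajectories, primary longitudinal analyses will focus on generalized linear mixed models". The reasons given are missing data and non-normal outcomes. The Discussion says, without limiting it to any outcome, that "missing data will be handled via generalized linear mixed models".
- **Sample size.** Sample Size Estimation assumes "an effect size f=0.15, and a correlation between baseline and follow-up measures of 0.5".
- **Weights.** The Data Analysis Plan adds, also without restriction, "Results will be weighted by age, gender, and region".

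**The concern.** The mixed model is preferred for two reasons, missing data and non-normal outcomes, and both apply to the 0-100% primary items. Yet the only rule whose wording reaches those items is the general group-comparison rule.

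Three things are at stake:

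- **The pretest.** The usual tests under that rule compare groups at one visit and leave out the pretest value, although the trial was sized on its correlation with follow-up.
- **Missing values.** Such tests need an observed value at the visit, so they cannot deliver the Discussion's promise on missing data.
- **The estimand.** A preliminary test run on the trial data decides whether the primary comparison is of means or of ranks.

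The weighting sentence, as written, also reaches the randomised contrast, where weights to population margins add variance.

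**Working it through.** **1. The plan's own figure.** Inputs from Sample Size Estimation: f = 0.15, α = 0.05, power 90%, correlation 0.5. The four arms come from Participant Recruitment and Randomization. Two measurements is an assumption; it is the choice that reproduces the figure.

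Repeated-measures ANOVA, within-between interaction:
λ = f² × N × m / (1 − ρ) = 0.0225 × 164 × 2 / 0.5 = 14.76, with df 3 and 160. Power = 0.905.

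At N = 160, the next smaller multiple of four, power is 0.897, so 164 is reproduced exactly. Then 164 × 2 = 328, and 328 / (1 − 0.5) = 656. The 164 therefore uses the correlation directly, through the divisor 1 − ρ. A test comparing groups at a single visit does not use it.

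**2. Would the gate trigger?** The article gives no distribution for the 0-100% items, so five shapes were assumed. Shapiro-Wilk rejection at the 5% level, 400 runs each:

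| Assumed shape | n = 164 | n = 278 | n = 666 | n = 1112 |
|---|---|---|---|---|
| Mean 50, SD 30, clipped | 99% | 100% | 100% | 100% |
| Mean 50, SD 20, answers in tens | 100% | 100% | 100% | 100% |
| Skewed (beta 0.5, 2) | 100% | 100% | 100% | 100% |
| 40% zeros | 100% | 100% | 100% | 100% |
| Mean 50, SD 20, clipped (near normal) | 5% | 5% | 41% | 94% |

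The gate is very likely to trigger for skewed, heaped or zero-heavy answers, but not for a near-normal item at the size of one arm.

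**3. What leaving out the pretest costs.** Assumptions: two-arm contrast, two-sided 0.05, pretest-posttest correlation 0.5, standardised difference 0.20 or 0.30 (0.30 being 2f), 3000 runs. Sizes from the article: 666/4 ≈ 166 completers per arm, with PNF-A and PNF-B together 666/2 = 333; and 1112/4 = 278 enrolled per arm. The clipped item has mean 30, SD 25, limited to 0-100.

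| Setting | Difference | Mann-Whitney | t test | Pretest-adjusted |
|---|---|---|---|---|
| Clipped item, 333 v 166 | 0.20 | 55% | 55% | 68% |
| Clipped item, 333 v 166 | 0.30 | 87% | 88% | 95% |
| Normal, 164 per arm | 0.20 | 42% | 43% | 56% |
| Normal, 164 per arm | 0.30 | 74% | 76% | 88% |
| Normal, 278 per arm | 0.20 | 63% | 65% | 77% |
| Normal, 278 per arm | 0.30 | 94% | 94% | 99% |

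At completer sizes the gap between Mann-Whitney and the adjusted model is 8 to 14 points. It shrinks to 5 where power is already near its ceiling. Mann-Whitney and the t test differ by 0 to 2 points here (up to about 3 in a repeat of the runs), so nearly all the loss comes from omitting the pretest, not from ranking. The reason is that adjustment multiplies the residual variance by 1 − ρ² = 1 − 0.25 = 0.75.

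**4. Missing values at 12 weeks.** 1112 − 666 = 446, and 446/1112 = 40.1%. No attrition figure is given for the immediate posttest.

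**5. Weights.** Effective N falls by 1 − 1/(1 + CV²). The article gives no weight distribution, so the CVs are assumed: 0.3 gives 8%, 0.5 gives 20%, 0.7 gives 33%.

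**The case against.** A reader might infer that the plan prescribes unadjusted rank tests on completers for all primary outcomes and reserves mixed models for the secondary ones. The article does not say that.

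- The plan item and the yes/no items are categorical and never meet the normality gate.
- No rank test is named, and some nonparametric methods do use covariates or change scores.
- MANCOVA is listed, and the Data Analysis Plan says observed variables will be controlled when PNF is evaluated.
- The Discussion's missing-data sentence covers every outcome.
- Study Design presents the immediate effect as the main motivational question and 12 weeks as maintenance, so the 40.1% does not bear on the immediate comparison.
- The full analysis plan may name the models and limit the weights to the prevalence estimates.

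Much of this stands, and it sets the limits of the point. It does not remove it. The covariate sentence is framed as a check on baseline balance and names no pretest adjustment. MANCOVA sits under the same gate. The Discussion's statement cannot hold for an item analysed by t test or its usual rank counterpart. A stated rule for group comparisons also differs from a detail left for later: as worded, it is the one that reaches these items.

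**Conclusion.** The point holds as a mismatch within the stated plan. The general group-comparison rule is the only one that reaches the primary items, and it names neither pretest adjustment nor a longitudinal model for them. That does not fit the sample-size basis or the Discussion's account of missing data.

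If the rule is followed with standard two-sample tests, the cost is roughly 8 to 14 points of power at differences of 0.20 to 0.30 and about the completer sizes, assuming a correlation of 0.5. The 12-week comparison would also leave out 40.1% of those enrolled. Removing the gate alone would recover almost nothing; the gain comes from using the pretest. It would, however, stop a preliminary test from choosing what is estimated.

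It is not supported to say that the gate is certain to trigger, since that depends on the shape of the answers, or that unadjusted completer analysis is the declared plan. The loss from weighting is illustrative only. The change should be made, but it is not a fatal flaw.

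**What to change.** 1. Drop the normality gate for the efficacy analysis.
2. For PNF (A and B together) versus the assessment group, use a linear mixed model with robust standard errors for each 0-100% item and a proportional-odds mixed model for the three-category plan item. Model posttest and 12 weeks together, adjust for the pretest, and include every participant in these arms with any post-randomisation value.
3. Analyse comparisons with the delayed assessment group separately and without pretest adjustment, because that group has no pretest.
4. Reconcile the Data Analysis Plan with the Discussion by stating which outcomes the mixed models cover.
5. State that the age, gender and region weights apply to the prevalence estimates of the first objective, with weighted efficacy results as a sensitivity analysis.

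The cost is plan wording and modest extra modelling. The pretest data are already collected and no further participants are needed. Because the article reports analyses under way as of January 2026, the change should be dated and described as made before or after sight of the primary comparisons, whichever is true.

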### Primary Outcomes

Intention to change gambling or trading behavior was assessed through 3 ad hoc items. Participants answered a dichotomous item (yes or no) adapted to their chosen behaviors during the screening phase (eg, “In the last year, have you thought about reducing or quitting [financial asset trading/gambling]?”). Participants then reported the likelihood of engaging in gambling or trading over the next 12 months on a scale from 0% (very unlikely) to 100% (very likely). A third item asked participants to specify their actual plan regarding their behavior (not reducing or stopping, reducing or stopping in the following 6 months, and reducing or stopping in the following 30 days), with the latter 2 items administered at baseline, postintervention assessment, and follow-up.

Intention to seek treatment was also measured (at pretest, posttest, and at 12-week follow-up) using a likelihood item (0%‐100%). Help-seeking behaviors were additionally assessed at baseline using a question adapted from the study by Rodda et al [65] about prior help seeking (eg, “Have you ever sought professional help or advice, support from family or friends, or taken any self-directed actions to reduce your [gambling/trading] behavior?”). If answered affirmatively, participants completed an adaptation of the Help-Seeking Questionnaire [65], which includes items assessing self-directed, distance-based, and face-to-face help-seeking behaviors (eg, reading forums, browsing informational websites, and talking to a gambling counselor).

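### Single-step Bonferroni is valid but needlessly conservative: Holm's step-down gives the same familywise error control and never rejects less, for a modest gain in power at little cost

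*Protocol article*

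**What the plan says.** The Data Analysis Plan names one multiplicity method: "To control for type I error due to multiple comparisons, the Bonferroni correction will be applied". The sentence closes a description of descriptive analyses and group comparisons (chi-square, t test, ANOVA). In the text shown it is not tied to a particular set of hypotheses.

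Several motivational items could fall under it. The Primary Outcomes section describes three items on intention to change. Two of these, the likelihood of engaging and the current plan, are repeated at baseline, postintervention and follow-up. The section adds: "Intention to seek treatment was also measured", at the same three occasions. So three repeated items bear on the efficacy question.

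The Sample Size Estimation section treats multiplicity separately. It arrives at 164 participants for a single outcome at 90% power, and then states: "Given the evaluation of multiple outcomes, a minimum effective sample size of 328 was required".

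**The concern.** Bonferroni compares every p-value with 0.05/K. Holm compares the smallest with 0.05/K, the next with 0.05/(K−1), and so on, stopping at the first failure. Its thresholds are never stricter than Bonferroni's, it needs no assumption about correlation, and it keeps familywise error at or below 5%. This is true for any family, so the comparison does not depend on how the family is defined.

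If the feedback raises motivation generally, as the Introduction and aims suggest, more than one item should respond. That is the situation in which Holm gains. A real effect on a second or third item could be reported as not significant under Bonferroni when the same data at the same familywise error rate would support it.

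**Working it through.** **Inputs from the protocol article**
- Sample Size Estimation: "Assuming an α error of 5%, an effect size f=0.15, and a correlation between baseline and follow-up measures of 0.5"; 90% power; 164 participants for one outcome, doubled to 328, then 656 after 50% attrition.
- Participant Recruitment and Randomization, and Sample Size Estimation: four equal arms (25% each). Study Design: two of the four are feedback sequences (PNF-A and PNF-B), and one control arm has no pretest.
- Results: 1112 enrolled, 666 completers at 12 weeks.

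**Assumptions not in the document**
- K tests with normal statistics, equally correlated at 0.5. The article's 0.5 is between baseline and follow-up, not between items.
- All K items affected equally, unless stated otherwise.
- Normal outcomes, which is an approximation because the plan item has three ordered categories.

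**Step 1. The plan's own figure.** For a within-between interaction, λ = f²·N·m/(1−ρ). With 4 groups and m = 2 measurements (both assumed), λ = 0.0225 × 164 × 2/0.5 = 14.76, and power is 90.5%. So 164 reproduces; 2 × 164 = 328 and 328/0.5 = 656.

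**Step 2. Normal model at N = 164.** 90% power at two-sided 5% means a statistic with mean 1.96 + 1.28 = 3.24. For three items, per-item power is 80% (Bonferroni) v 87% (Holm), and power for all three is 61% v 77%. This ignores the doubling for multiple outcomes.

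**Step 3. The same model at N = 328.** The mean becomes 3.24 × √2 = 4.58.

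| Items | Per item: Bonferroni v Holm | All items: Bonferroni v Holm |
|---|---|---|
| 2 | 99.1% v 99.5% | 98.2% v 99.2% |
| 3 | 98.6% v 99.5% | 96.3% v 98.8% |
| 4 | 98.2% v 99.4% | 94.1% v 98.4% |

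For three items the gain is about 1 point per item and 2.5 points for all three.

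**Step 4. Feedback versus assessment control at follow-up.** With equal retention across arms (assumed), 666 completers give about 333 v 166. Adjusting for baseline with correlation 0.5, the mean of the statistic is d/√[(1 − 0.5²)(1/333 + 1/166)] = d/0.0823. At d = 0.30 this is 3.65. (For two equal groups d = 2f, so f = 0.15 corresponds to d = 0.30.) Three items:

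| d | Mean | Per item: Bonferroni v Holm | All three: Bonferroni v Holm |
|---|---|---|---|
| 0.30 | 3.65 | 90% v 94% | 77% v 88% |
| 0.25 | 3.04 | 74% v 81% | 53% v 69% |
| 0.20 | 2.43 | 52% v 59% | 27% v 42% |

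**Step 5. Only one of three items moves.** In the Step 2 setting its power is 80.2% v 80.3%, so the gain is about 0.1 point.

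**The case against.** The strongest reply is that nothing here is wrong. Bonferroni is valid, conservative and named in advance, and the existence of a more powerful procedure is a refinement. That stands.

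The sample size also already allows for multiplicity. Under the 4 × 2 interaction of Step 1, per-item power at 328 with Bonferroni is 99.5%, 99.3% and 99.0% for two, three and four items. Holm then adds only 0.3 to 0.8 points, and at 666 both methods are at about 100%. This stands only in part. The 4 × 2 layout is an assumption, and the delayed assessment arm has no pretest, so it cannot contribute a pre-post change. On the contrast that answers the efficacy question, at the effect size the plan itself uses, power is not near 100% and the two methods differ by about 4 points per item.

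A reader might infer that Bonferroni gives power away for nothing, or costs some 16 points for detecting all three items. The documents support neither. The 16 points (61% v 77%) belong to N = 164, which the plan doubles. Bonferroni also offers simple simultaneous intervals, which Holm does not. A reader might also infer that the correction is meant for the primary items. The sentence does not say so, and it could refer to comparisons between arms.

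**Conclusion.** The point holds as a cheap improvement, not as the correction of an error. That Holm is never worse on rejections is a theorem and needs no assumptions about this trial. The size of the benefit does need them. With three items all affected, it runs from about 1 point per item at the planned 328 in the simple normal model to about 4 points on feedback versus assessment control at d = 0.30, and 7 to 8 points at d = 0.20 to 0.25. For detecting all three items the gain on that contrast is about 11 points at d = 0.30 (77% v 88%) and 15 to 16 points at the smaller effects. Smaller effects deserve attention, because the article concedes that no prior studies exist for these outcomes and takes its effect size from trials on other gambling outcomes. If only one item responds the gain is near zero, and with large effects it vanishes.

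**What to change.** Replace the Bonferroni sentence with: *Familywise error at 5% (two-sided) is controlled by the Holm step-down procedure; Holm-adjusted p-values are reported.* Report 95% confidence intervals alongside, labelled as unadjusted for multiplicity.

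The Results section says that data collection is complete and analyses are ongoing as of January 2026. The change must therefore be dated, disclosed and documented as made before treatment comparisons are seen. If they have already been seen, keep Bonferroni as the stated method and report Holm as a labelled sensitivity analysis.

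The cost is one sentence, one line of code and the disclosure. The downside is that Holm has no simple matching simultaneous intervals, so an unadjusted interval may exclude the null when the adjusted test does not reject. The Data Analysis Plan promises no simultaneous intervals, so no stated commitment is lost.

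### Covariate control is justified as a way to balance groups and confirm randomisation; its real value is precision, and the plan does not commit to pretest adjustment of the primary items

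*Protocol article*

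**What the plan says.** In the Data Analysis Plan, the only rule on covariates for the PNF evaluation is that "observed variables will be controlled to ensure balanced baseline characteristics between control and experimental groups, thus confirming randomization integrity". The variables are not named.

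The same section says that "group comparisons will be performed using chi-square tests for categorical variables", with t tests and ANOVA for continuous variables; MANOVA and MANCOVA are listed under ANOVA. Generalized linear mixed models appear as the longitudinal method for gambling and trading trajectories, which belong to the secondary outcomes. The Discussion also names them as the way to handle missing data.

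The material for pretest adjustment exists. Primary Outcomes describes three intention items, "with the latter 2 items administered at baseline, postintervention assessment, and follow-up". The 0-100% likelihood of seeking treatment is also measured at pretest, posttest and 12 weeks. Under Study Design, the PNF and assessment arms have a pretest and the delayed assessment arm does not. Under Participant Recruitment and Randomization, allocation equalises arm counts without regard to baseline characteristics.

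**The concern.** The stated purpose is wrong on both counts. Adjustment leaves the groups as they are; it changes what the estimate is conditioned on. Neither adjustment nor observed balance shows that allocation was carried out properly. That is established from the allocation algorithm and its log.

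The purpose matters because it steers the choice of covariates. If balance is the aim, a variable that looks balanced seems to need no control, and the participant's own pretest value could be left out on that ground. If precision is the aim, the pretest value goes in regardless, because it is likely to be the strongest predictor of the posttest value. At stake is the width of the interval around the PNF effect on the primary motivational items, and a covariate set that should not be open to choice once the data are in view.

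**Working it through.** **1. The plan's own figures.** Sample Size Estimation gives α of 5%, "an effect size f=0.15", "a correlation between baseline and follow-up measures of 0.5" and 90% power. A repeated-measures within-between interaction with k = 4 groups and m = 2 times has noncentrality λ = f²·N·m/(1−ρ), with df (k−1)(m−1) and (N−k)(m−1).
- At N = 162, λ = 0.0225 × 162 × 2 / 0.5 = 14.58 with 3 and 158 df, and power is 0.901. Rounding up to four equal groups gives the stated 164.
- 2 × 164 = 328, as stated ("a minimum effective sample size of 328 was required"). 328/(1 − 0.5) = 656, and 656/4 = 164 per condition.

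These figures reproduce and are not in dispute. The test that reproduces them uses the pretest.

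**2. Variance of the PNF effect under three analyses** (posttest-only = 1; equal variances at both times; r = pretest-posttest correlation). ANCOVA on the pretest: 1 − r². Change score: 2(1 − r).

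| r | ANCOVA | Change score | Posttest only | Participants needed relative to ANCOVA: posttest only / change score |
|---|---|---|---|---|
| 0.3 | 0.91 | 1.40 | 1 | 1.10 / 1.54 |
| 0.5 (plan) | 0.75 | 1.00 | 1 | 1.33 / 1.33 |
| 0.7 | 0.51 | 0.60 | 1 | 1.96 / 1.18 |

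At r = 0.5 the standard error is multiplied by √0.75 = 0.866. The values 0.3 and 0.7 are assumptions that show the range.

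**3. What that means in power.** Assumptions: two-sided 5%, d = 2f = 0.30 for a two-group contrast, and PNF-A and PNF-B pooled against the assessment arm (2:1). Power ≈ Φ(d/SE − 1.96).
- Effective sample of 328, so 164 versus 82: SE = √(1/164 + 1/82) = 0.135. Power is 0.60 unadjusted and 0.73 adjusted at r = 0.5 (0.64 at r = 0.3, 0.87 at r = 0.7).
- The 666 completers, if spread evenly over the arms (about 333 versus 166): 0.885 unadjusted, 0.954 adjusted.
- All 1112 enrolled, if spread evenly (556 versus 278), as an upper limit for the immediate posttest: 0.983 unadjusted, 0.997 adjusted.

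**4. What happens if control follows observed balance.** Simulation with 20,000 runs, 164 versus 82, r = 0.5:

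| Rule | Empirical SE (d = 0.30) | Power (d = 0.30) | Type I error (d = 0) |
|---|---|---|---|
| Never adjust | 0.134 | 0.60 | 0.049 |
| Adjust only if the baseline test is significant | 0.130 | 0.61 | 0.044 |
| Always adjust | 0.116 | 0.72 | 0.051 |

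Adjusting on imbalance keeps almost none of the gain. It does not inflate type I error here.

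**5. Why baseline tests cannot confirm randomisation.** With sound allocation and k independent baseline variables tested at 5%, the chance of at least one significant difference is 1 − 0.95^k: 23% for k = 5, 40% for k = 10 and 64% for k = 20.

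**The case against.** The strongest reply is that the sentence is only loosely worded. It says variables will be controlled. It does not say that covariates are picked after balance has been examined, or that baseline tests trigger adjustment. MANCOVA, a covariate-adjusted method, is on the list, and nothing excludes the pretest value. The sample size itself corresponds to an analysis that uses the pretest. A journal article may leave the covariate list and the model for each outcome to the full plan. Describing balance is also reasonable, given least-fill allocation with random choice only for ties and 59.9% retention.

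Much of this stands. A reader might infer data-driven covariate selection, but the text does not state it. A reader might infer an unadjusted primary analysis, but with MANCOVA named the document does not commit to one. The absence of a covariate list is not the point raised here. The variance formula suits the 0-100% items and does not carry over directly to the three-category plan item. The thought-about-reducing item and the prior help-seeking question are described at baseline only, so not every primary item has a pretest-posttest pair.

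What the reply does not rescue is the stated purpose, which is wrong on any reading. Nor does it supply a commitment to pretest adjustment: MANCOVA is named without covariates, and the mixed models are introduced for the secondary behavioural trajectories.

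**Conclusion.** The point holds in limited form. The article gives the wrong reason for covariate control and does not commit to the adjustment that would use the pretest data it collected on the primary items. For the 0-100% likelihood items at r = 0.5, the potential cost is a variance one third larger (1/0.75 = 1.33). That cost arises only if the analysis is posttest-only or a change score; control triggered by imbalance recovers little of it. It is zero if the pretest is always in the model.

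The size rests on several assumptions. The 0.5 is a planning value for gambling-related outcomes between baseline and follow-up, and the correlation for these ad hoc items at the immediate posttest is unknown. The value d = 0.30 and the 2:1 contrast are also assumed, and the planned weighting is ignored. The power figures illustrate the gain; d = 0.30 is not the contrast in the interaction test that reproduces 164, so they do not show that the trial was underpowered. Enrolment of 1112 against a target of 656 softens the consequence further. A reader might also infer a false-positive problem, but the simulation shows none. This is a moderate matter of precision and of a wrong statement, and it is cheap to correct.

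**What to change.** Replace the sentence on controlling observed variables with a rule along these lines:
- Each primary item with a pretest value is analysed by a regression suited to its scale (for example linear for the 0-100% items, ordinal for the plan item). In PNF versus the assessment arm it is always adjusted for that pretest value and for a short fixed list of eligibility variables, such as age, sex, psychological distress and past-60-day gambling or trading.
- Comparisons that include the delayed assessment arm, which has no pretest, are adjusted for the eligibility variables only.
- Baseline characteristics are described by arm without significance tests. The claim that covariate control confirms randomisation is removed; allocation integrity is reported from the allocation procedure.

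Data collection is complete and analyses are under way, so the rule should be dated, declared as added at this stage, and fixed before primary results are reported. The cost is wording and model specification only: the pretest values and eligibility variables have already been collected, and no sample-size figure changes.
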